**Table 8-4 Minimum detectable differences in mean response magnitudes between two arms (of size 30)**

| True mean response* Arm 1 | Minimum detectable mean response* Arm 2 |           |
|---------------------------|-----------------------------------------|-----------|
|                           | 80% power                               | 90% power |
| 100                       | 191                                     | 209       |
| 200                       | 382                                     | 418       |
| 300                       | 572                                     | 627       |
| 400                       | 763                                     | 836       |
| 500                       | 953                                     | 1045      |

\*Observed SFU per ELISpot well ( $\sim 2 \times 10^5$  PBMC). Response rate conventionally reported per  $10^6$  PBMC.

## 8.5 Statistical analysis

All data from enrolled participants will be analyzed according to the initial randomization assignment regardless of how many vaccinations they received. Since enrollment is concurrent with receiving the first vaccination, all participants will have received one vaccination and therefore will provide some safety data. The analysis is not strictly intent-to-treat but is approximately so; that is, individuals who are randomized but not enrolled do not contribute data and hence are excluded. Because of the brief length of time between randomization and enrollment—typically no more than 4 working days, according to the *HVTN Manual of Operations (HVTN MOP) (Study Operations >Enrollment >Randomization)*—very few such individuals are expected.

If a participant receives the wrong randomization assignment, analyses for immunogenicity will be done both according to the assignment they should have received and also according to the assignment they actually received. It is expected that there should be very few such cases.

Analyses for primary endpoints will be performed in SAS. All other descriptive and inferential statistical analyses will be performed using SAS, S-Plus, and/or R statistical software.

No formal multiple comparison adjustments will be employed for safety endpoints or secondary immunogenicity endpoints. However, multiple measurements of a specific type of immune response may be treated as a collection of hypotheses that requires a multiplicity adjustment. For example, determination of cellular immune responses to several different HIV-1 peptide pools as measured by the IFN- $\gamma$  ELISpot assay may entail a multiplicity adjustment to account for the multiple peptide pools considered.

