## Overview

### Title

A phase Ib clinical trial to compare the safety, tolerability, and immunogenicity of an HIV-1 adenoviral vector boost administered intramuscularly, intradermally, or subcutaneously after an HIV-1 DNA plasmid vaccine prime administered intramuscularly to healthy adenovirus type 5 seropositive HIV-1-uninfected adults

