# **STUDY DESIGN**

## **5 Study objectives**

### **5.1 Primary objectives**

- To investigate the safety and tolerability of a 4-plasmid DNA prime followed by an Ad5 boost with the boost administered IM, ID, or SC.
- To compare ID vs. IM and SC vs. IM routes of Ad5 boost administration to determine if either the ID or SC route is superior to IM in eliciting vaccine-induced HIV-specific T-cell responses as assessed by the magnitude of IFN- $\gamma$  ELISpot responses 4 weeks after the Ad5 boost.

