#### **8.5.3 Safety analysis**

##### *Reactogenicity*

The number and percentage of participants experiencing each type of reactogenicity sign or symptom will be tabulated by severity. For a given sign or symptom, each participant's reactogenicity will be counted once under the maximum severity for all injection visits.

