#### **8.5.4 Immunogenicity analysis**

For the statistical analysis of immunogenicity endpoints, all data from enrolled participants will be used according to the initial randomization assignment regardless of how many injections they received. The only exception will be to exclude data from HIV-infected

participants at or post infection. Thus, for HIV-infected participants, only immunogenicity data from samples drawn prior to HIV infection will be included in the analysis.

If assay data are qualitative (i.e., positive or negative), then analyses will be performed by tabulating the frequency of positive response for each assay by arm at each time point that an assessment is performed. Binomial response rates will be presented with their corresponding exact 95% confidence interval estimates.

To compare the response rates of any two vaccine arms, a significant difference will be declared if the 2-sided 95% confidence interval for the difference in response rates between the two arms excludes 0. If assays are run at multiple time points, the probability of observing at least one positive response by a given time point and the probability of observing more than one response by a given time point will be estimated, with corresponding confidence intervals, for each vaccine arm using maximum likelihood based methods [53]. Missing responses will be assumed to be missing at random (i.e., conditional on the observed data the missingness is independent of the unobserved responses).

For continuous assay variables, overall differences between arms at a specific time point will be tested by a 2-sample t-test if the data appear to be normally distributed after certain power or logarithm transformations, or by utilizing the nonparametric Wilcoxon rank sum test if the transformed data are not normally distributed. More sophisticated analyses employing repeated measures methodology (for example, repeated measures ANOVA or generalized estimating equations) may be utilized to incorporate immune responses over several time points. However, inference from such analyses would be limited by the small sample size of this study. All statistical tests will be 2-sided and will be considered statistically significant if  $p \leq 0.05$ . Graphical descriptions of the longitudinal immune responses will also be given.

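### A participant boosted by the wrong route is re-analysed by route received for immunogenicity but not for safety, so post-boost safety data are tabulated only under a route that was not given

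*Protocol*

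**What the plan says.** Section 8.5 of the protocol gives one general rule: "All data from enrolled participants will be analyzed according to the initial randomization assignment regardless of how many vaccinations they received". The next sentence refers to the safety data that every enrolled participant will provide, so the rule covers safety as well as immunogenicity.

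The same section then deals with allocation errors: "If a participant receives the wrong randomization assignment, analyses for immunogenicity will be done both according to the assignment they should have received", and a second time by what was actually received. It adds: "It is expected that there should be very few such cases".

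Section 8.5.3 describes the safety tabulations and has no as-received rule for reactogenicity, adverse experiences or laboratory values. For reactogenicity it says that "each participant's reactogenicity will be counted once under the maximum severity for all injection visits".

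The first primary objective in Section 5.1 is: "To investigate the safety and tolerability of a 4-plasmid DNA prime followed by an Ad5 boost with the boost administered IM, ID, or SC". The study title goes further and says the trial is "to compare the safety, tolerability, and immunogenicity of an HIV-1 adenoviral vector boost administered intramuscularly, intradermally, or subcutaneously".

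**The concern.** The three groups receive the same DNA prime (Schema, Sections 8.4 and 12.1) and differ only in the route of the Month 6 Ad5 injection. An allocation error therefore matters only through the route of that injection, which is the exposure whose safety the trial sets out to describe.

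The authors anticipated the error and wrote a rule for it, but the rule leaves safety out. A participant assigned to one route and boosted by another would have post-boost reactions, adverse events and laboratory values counted under the assigned route alone. The route actually given would show nothing.

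Route-specific safety data are scarce. Section 1.2 knows of no report of subcutaneous use of a recombinant adenoviral vector, and Section 4 describes the first trial of this vaccine by the ID and SC routes as still to open. One misattributed event could be a noticeable part of the evidence on a route.

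**Working it through.** **1. Which data the rule covers**

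| Data | By assigned arm | By route received |
|---|---|---|
| Immunogenicity | Yes (8.5, 8.5.4) | Yes, after an allocation error (8.5) |
| Reactogenicity, adverse events, laboratory values | Yes (8.5, all data) | Not provided (8.5, 8.5.3) |

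The second row follows from a stated rule and a stated limit on its exception.

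**2. The plan's own intervals**

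Table 8-2 gives exact 95% intervals for arms of 30. With no events, the exact upper bound is 1 − 0.025^(1/n). For n = 30 this is 1 − 0.025^(1/30) = 11.6%, as printed. For 1/30 the Clopper-Pearson interval is [0.1, 17.2%], also as printed. All six rows of the table reproduce.

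**3. One misplaced rare event**

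Suppose one IM-assigned participant is boosted ID and has, after the boost, the only event of its kind in those two arms. Everyone else receives the assigned route. By route received, the denominators become 30 − 1 = 29 for IM and 30 + 1 = 31 for ID.

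| Route | As the plan is written | By route received |
|---|---|---|
| IM | 1/30 = 3.3% [0.1, 17.2%] | 0/29 = 0% [0, 11.9%] |
| ID | 0/30 = 0% [0, 11.6%] | 1/31 = 3.2% [0.1, 16.7%] |

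The pooled result over 90 participants does not change. Only the attribution to route does.

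**4. Common reactions**

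Suppose m IM-assigned participants are boosted by a route whose true reaction rate is p1, against p0 for IM. The expected shift in the assigned IM arm's post-boost rate is m × (p1 − p0)/30. The protocol gives no route-specific rates, so a difference of 23 to 30 percentage points is assumed here.

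- m = 1: 23/30 = 0.8 to 30/30 = 1.0 points.
- m = 3: 3 × 23/30 = 2.3 to 3 × 30/30 = 3.0 points.

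In the planned reactogenicity table the shift would be smaller still. Each participant is counted once, at the maximum over all four injections, so a boost reaction changes an entry only if it exceeds that participant's worst reaction to the three DNA primes. In VRC 004, 19 of 20 recipients of 4 mg DNA had some local symptom (14 mild and 5 moderate, Table 4-2).

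**The case against.** **Rarity and safeguards.** The protocol expects very few such cases. Section 12.2 requires the route on the syringe label, and the ID boost uses a different vial strength, volume and syringe from the other two. This stands for ID. It is weaker for IM against SC: Sections 12.2.5, 12.2.7 and 12.3.2 give both the same vial strength, the same 1 mL volume and the same syringe sizes, and allow a 23 gauge needle for either.

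**Descriptive safety analysis.** Section 8.5.3 plans tabulations, listings and boxplots, with no test between arms. The safety objective speaks of investigating rather than comparing; the comparison of safety appears in the title. This limits the consequence, but the tables are still read by route.

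**Participant protection.** The pause rules in Table 13-2 count participants without regard to arm, and the Safety Monitoring Board sees individual serious event reports. This stands: the point concerns attribution in the analysis, not detection during the trial.

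**The SAP may add a table.** It may, but the protocol rule as it stands points the other way.

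A reader might infer more than the document supports:

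- *That 8.5.4 contradicts 8.5.* Section 8.5.4 states: "The only exception will be to exclude data from HIV-infected" participants' data from infection onward. That exception concerns which data are excluded. A supplementary as-received analysis excludes nothing, so the two sections are compatible.
- *That no immunogenicity result is primary.* Sections 8.5 and 8.5.4 both make the assigned arm the governing rule; the as-received analysis is an addition to it.
- *That every misrouted participant with an event moves an arm by 1/30.* That holds for a rare post-boost event, but not generally for reactogenicity, because of the maximum over all injections.
- *That ID and SC are known to differ.* Section 1.1 reports more local reactions by ID or SC than by IM in many studies of other vaccines, usually mild, with no overall difference in systemic reactions or serious events. It does not contrast ID with SC.

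**Conclusion.** The point holds as a limited one that is worth correcting. Section 8.5 fixes safety to the assigned arm and confines the as-received analysis to immunogenicity, so safety data after a misrouted boost are tabulated only under a route that was not given.

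For common reactions the effect is small: about 1 percentage point per case under an assumed route difference of 23 to 30 points, and less under the maximum-severity count. It matters for a rare or severe post-boost event, which is how Section 8.4.1 frames the safety sample size. There, one case moves the upper bound for the route not given from 11.9% to 17.2%, and lowers it for the route given from 16.7% to 11.6%. The example assumes one misrouted participant who has the only event of its kind in the two arms. The protocol gives no expected number of such errors.

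**What to change.** In Sections 8.5 and 8.5.3, state that for any participant boosted by a route other than the one assigned, reactogenicity, adverse events and laboratory values after the Month 6 injection are tabulated by the route actually received. At minimum, present them both ways, as is already planned for immunogenicity. Data before the boost can stay under the assigned arm, since the prime is the same in all groups. Section 8.5.4 needs no change.

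The cost is one or two sentences, plus a small amount of extra tabulation if such a case occurs. That tabulation has to separate post-boost from post-prime data, which the reactogenicity table in 8.5.3 does not now do, and the affected participant would sit under different routes before and after Month 6. Visits, sample size and data collection do not change.

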#### **8.5.1 Analysis variables**

The analysis variables consist of baseline variables, safety variables, immunogenicity variables, and social impact variables for primary and secondary objective analyses.

#### **8.5.2 Baseline comparability**

Groups will be compared for baseline characteristics including demographics and laboratory measurements, using descriptive statistics.

#### **8.5.3 Safety analysis**

##### *Reactogenicity*

The number and percentage of participants experiencing each type of reactogenicity sign or symptom will be tabulated by severity. For a given sign or symptom, each participant's reactogenicity will be counted once under the maximum severity for all injection visits.

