**Table 4-2 Reactogenicity of HIV-1 multiclade DNA vaccine at 4 mg in VRC 004**

| 4 mg DNA vaccine Experience | VRC 004 Biojector® N=20 |
|-----------------------------|-------------------------|
| Local Symptoms       |                         |
| None                        | 1 (5.0%)                |
| Mild                        | 14 (70.0%)              |
| Moderate                    | 5 (25.0%)               |
| Severe                      | 0                       |
| Systemic symptoms    |                         |
| None                        | 5 (25.0%)               |
| Mild                        | 11 (55.0%)              |
| Moderate                    | 4 (20.0%)               |
| Severe                      | 0                       |

#### 4.1.2 Protocol HVTN 052

HVTN 052 (N=180; randomized 120 to vaccine and 60 to placebo schedules) is the largest study with the 4-plasmid DNA vaccine, but study results remain blinded. Sixty-one percent of all participants (including placebo recipients) experienced mild or moderate symptoms of systemic reactogenicity (malaise, myalgia, headache, nausea, vomiting, chills, or arthralgia), the vast majority of which were mild. Local reactogenicity was reported by 88% of all participants with the worst severity usually mild, less frequently moderate, and in one case reported as severe. The severe injection site pain started 30 minutes after vaccination, was mild by the following day and resolved in 4 days. Other adverse events requiring expedited reporting but assessed as unlikely to be related to vaccination have included one case of newly diagnosed diabetes mellitus and one grade 3 asymptomatic thrombocytosis in a subject with an elevated pre-enrollment platelet count. An unblinded review of HVTN 052 safety data by the HVTN Safety Monitoring Board in February 2005 indicated that there were no significant differences in adverse events (AEs) or serious adverse events (SAEs) across treatment groups.

#### 4.1.3 Protocol RV 156

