## 8.4 Accrual and sample size

Recruitment will target 90 healthy, HIV-uninfected adult participants. This study will consist of 3 groups. All groups will be enrolled in parallel and randomized to receive DNA prime administered via IM injection using Biojector® and adenoviral vector boost administered via IM, ID, or SC injection using needle and syringe. See the study Schema for details.

Since enrollment is concurrent with receiving the first study vaccination, all participants will provide some safety data. Hence, sample size calculations for safety in Section 8.4.1 are based on the target sample sizes. However, this is not true of the immunogenicity data. Therefore the sample size calculations in Section 8.4.2 account for 10% of enrolled participants having missing data for the primary immunogenicity endpoints, an estimate based on previous HVTN and AIDS Vaccine Evaluation Group (AVEG) studies.

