### 8.4.1 Sample size calculations for safety

The goal of the safety evaluation for this study is to identify safety concerns associated with administration. Sample size calculations for safety are expressed in terms of the ability to detect rare events.

The ability of the study to identify rare events can be expressed by the maximum true rate of events that would be unlikely to be observed and the minimum true rate of events that would very likely be observed. Specifically, for each vaccine arm of the study ( $n=30$ ), there is a 90% chance of observing at least 1 event if the true rate of such an event is at least 8%; and there is a 90% chance of observing no events if the true rate is no more than 0.35%.

Probabilities of observing 0 or 2 or more events among arms of size 30 are presented in Table 8-1 for a range of possible true event rates. These calculations provide a more complete picture of the sensitivity of this study design to identify potential safety problems with the vaccine. In previous AVEG HIV vaccine trials, 3.5% of control participants experienced a serious adverse event; in HVTN vaccine trials (as of January 2006), about 1% of control participants had experienced such an event.

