#### **8.5.5 Social impact descriptive analysis**

Social impacts will be tabulated by type of event and impact on quality of life. The number and percentage of participants experiencing each type of social impact will also be tabulated by impact on quality of life. For this calculation, multiple events of the same type for a participant will be counted once under the maximum impact for all post-vaccination visits.

In addition, a listing will be generated of all participants who experienced a major disturbance of their quality of life due to study participation. The listing includes all social impacts experienced by these participants, descriptions of each impact, duration, impact on quality of life, actions taken by the participant and staff, and whether or not there was a resolution.

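### The only specified reactogenicity table pools the three common DNA primes with the boost, which dilutes differences between the IM, ID and SC routes

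*Protocol*

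**What the plan says.** Section 8.5.3 (Reactogenicity) tabulates each type of sign or symptom by severity. For a given one, a participant's "reactogenicity will be counted once under the maximum severity for all injection visits". No other reactogenicity table is described. Section 8.5.5 uses parallel wording for social impacts, which are "counted once under the maximum impact for all post-vaccination visits". This supports reading the reactogenicity rule as a maximum across visits and not one maximum per visit.

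The Schema and section 12.1 show that all three groups receive the same three DNA injections by Biojector (Months 0, 1 and 2). The groups differ only in the route of the single Ad5 injection at Month 6.

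The title says the trial is "to compare the safety, tolerability, and immunogenicity of an HIV-1 adenoviral vector boost administered intramuscularly, intradermally, or subcutaneously". Section 1 names safety data on the Ad5 vaccine by each route as part of its first goal. The primary safety objective in section 5.1 is worded more broadly: "To investigate the safety and tolerability of a 4-plasmid DNA prime followed by an Ad5 boost with the boost administered IM, ID, or SC".

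Section 13.1 has reactogenicity assessed after every vaccination, so boost-only data will exist.

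**The concern.** Everything that distinguishes the arms happens at one of four injection visits. A worst-grade summary over all four adds the same background of DNA reactions to each arm. A participant with a given grade after a DNA injection is already counted at that grade, and an equal or milder reaction to the boost then adds nothing to the table.

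This matters because local tolerability is the expected cost of the new routes. Section 1.1 reports that, in many of the studies it reviews, local reactions were more frequent after ID or SC than after IM injection, though generally mild and short-lived. Mild reactions are also common after the DNA prime, so the pooled maximum hides the boost's contribution most at that grade. Section 1.2 knows of no report of SC use of a recombinant adenoviral vector. Section 4 says that the first trial giving this vaccine ID or SC had yet to open. A clear description of reactions by boost route is therefore a main safety product of this trial.

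**Working it through.** **Plan's own figures.** The protocol attaches no number to this rule. The nearby safety figures reproduce at n = 30 per arm. In Table 8-1, the probability of no event at a 1% rate is 0.99^30 = 0.740. In Table 8-2, the upper limits are 11.6% for 0/30 and 4.0% for 0/90. Those tables are not in dispute.

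**Inputs.**
- Table 4-2 ("Reactogenicity of HIV-1 multiclade DNA vaccine at 4 mg in VRC 004", N = 20): any local symptom 19/20 = 95%, moderate local 5/20 = 25%, severe local 0; any systemic symptom 15/20 = 75%.
- Section 4.1.1: pain was the only local symptom graded moderate after DNA. The 25% therefore belongs to pain, and moderate erythema or induration was 0/20.
- Table 4-4, IM Ad5 booster (N = 14): moderate local 1/14 = 7%, severe local 0; any systemic symptom 9/14 = 64%.
- No ID or SC rates are given. Those below are hypothetical.

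**Formula.** Let p be the rate after the prime and b the rate after the boost, at a given grade or worse. If the two are independent, the pooled rate is 1 − (1 − p)(1 − b). The difference between two routes is then (1 − p) times the true boost difference. With complete overlap, the pooled rate is max(p, b).

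**Moderate pain.** Take p = 0.25, IM boost 0.07 and ID boost 0.40, and treat the 7% as pain. The true difference is 33 points.
- Independent: IM 1 − 0.75 × 0.93 = 0.3025; ID 1 − 0.75 × 0.60 = 0.55. Difference 24.75 points.
- Complete overlap: IM max(0.25, 0.07) = 0.25; ID max(0.25, 0.40) = 0.40. Difference 15 points.
- With a smaller ID rate of 0.27 (true difference 20 points): 0.4525 − 0.3025 = 15 points if independent, and 27 − 25 = 2 points with complete overlap.

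**Any-grade symptoms.** Tables 4-2 and 4-4 give only composites over all local or all systemic symptoms, while the planned table is per symptom. The composites are ceilings for p, so the results below show the strongest dilution that these data allow under independence.
- Any local, p = 0.95, boosts 50% vs 100% (both assumed): 50 points become 0.05 × 50 = 2.5 points (100 − 95 = 5 with complete overlap).
- Any systemic, p = 0.75, boosts 64% vs 94% (the second assumed): 30 points become 0.25 × 30 = 7.5 points (94 − 75 = 19 with complete overlap).

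For a single symptom p is lower and more of the difference survives. The documents do not allow a per-symptom figure.

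**Where nothing is lost.** For severe local reactions p = 0, so boosts of 0% vs 20% appear as 20 points. The same holds for moderate erythema or induration if the prime rate is 0, as in Table 4-2.

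**The case against.** The strongest reply has five parts.

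*The table still reflects the boost.* A reader might infer that the tabulation cannot show route differences at all. That goes too far. The arms are randomized and share the same prime, so a difference between arms beyond chance reflects the boost. It is attenuated: in the example, 25 of 33 points remain under independence. Severe reactions are not masked. This part of the reply stands.

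*The objective is met.* A reader might infer that the primary safety objective is defeated. Section 5.1 speaks of investigating the whole regimen, and a whole-regimen maximum does describe that. The comparison of boost routes comes from the title and the first goal in section 1. The mismatch is with those.

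*The sizes are hypothetical.* This is also true. The 40% ID rate is assumed, the prior data come from 20 and 14 participants, and 95% and 75% are composites that appear in no planned row. A reader might go on to express the dilution as lost power, but section 8.5.3 is descriptive and plans no reactogenicity test, so power is not a consequence for this plan.

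*The safety sample size.* A reader might infer that Tables 8-1 and 8-2 should use 27 boosted participants per arm. The 10% loss in section 8.4 concerns missing immunogenicity data, not missed boosts, and that section explains the use of the full number: "Since enrollment is concurrent with receiving the first study vaccination, all participants will provide some safety data". The change would also be trivial. The upper limit for no events would move from 11.6% to 12.8%, and the chance of at least one event at an 8% rate would be 1 − 0.92^27 = 89.5%, against the stated 90%.

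*A statistical analysis plan may add a boost table.* It may, and the data are collected. But the protocol does not leave the matter open. It states a counting rule, and that rule, followed as written, gives only the pooled table.

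**Conclusion.** The point holds as one of dilution and attribution. The single reactogenicity table in section 8.5.3 combines three injections common to all arms with the one that differs. It shrinks route differences for mild local and systemic symptoms and for moderate pain, and it leaves unclear which vaccine a reaction followed. Severe reactions, and moderate local signs that the prime did not cause, are largely unaffected.

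In the moderate-pain example, 33 points appear as about 25 under independence or 15 with complete overlap. This rests on the small prior trials in Tables 4-2 and 4-4, on treating the IM booster's 7% as pain, on an invented ID rate, and on the prior participants resembling this trial's Ad5-seropositive population. The direction needs less: some participants must react at the same grade to both prime and boost, more of them in the arm with more boost reactions. No error in the safety sample-size tables follows.

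**What to change.** In section 8.5.3, replace the single rule with wording such as:

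*For each sign or symptom, maximum severity will be tabulated separately for (a) the DNA injections and (b) the Month 6 Ad5 boost. Table (b) will be presented by randomized arm among participants who received the boost, with that number stated for each arm. ID-IM and SC-IM differences will be given with 95% confidence intervals, for description only. A table of maximum severity over all injection visits may be added as a supplement.*

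Using the randomized arm keeps table (b) in line with section 8.5. Restricting it to boosted participants conditions on an event after randomization in an open-label trial, which is why the number boosted per arm should be shown.

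The cost is one more set of tables. Section 13.1 already collects the data after each vaccination, so no procedure, visit or sample size changes. Tables 8-1 and 8-2 can stay as they are.
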